## Discussion

In this article the study design of a settings-based intervention targeting well-being, smoking and dropout among students in upper secondary vocational education is described; in a sample of approximately 22 % of all Danish technical and agricultural vocational schools. In addition, the representativeness of the convenience sample is determined. Because school dropout and health risk behavior represent major problems among students attending vocational education in Denmark and many other countries [49], there is a need for evidence-based intervention programs in the vocational school setting. Furthermore, students attending vocational education have less favourable health practices than the general population, and it is a more heterogeneous population than students attending general upper secondary education. The design of this intervention study takes account of these issues by adopting a comprehensive perspective on both health behaviour and the social environment at school.

### Study strengths and limitations

The strength of Shaping the Social is the relatively high response rate at the baseline survey, which may have been due to our efforts to collect data during school hours. Dropping out of school is a condition of the vocational school setting, which adversely affected the retention rates. However, the high submission of the personal identification number in the baseline survey makes it possible for us to link data to education registers at an individual level. Thus, we will be able to determine the intervention’s long-term effect on educational attainment.

The aspect that creates the intervention’s potential success (its settings-based comprehensiveness) also creates potential difficulties in analysing its effectiveness. The variety of factors that contribute e.g., to student well-being makes it challenging to clearly distinguish between successful and unsuccessful characteristics of the programme. The intervention’s comprehensiveness (establishment of new school practices and re-shaping existing practices) rules out a highly standardized intervention. This is addressed by collecting and analysing teacher data with respect to the school practices [42]. However, it proved infeasible to collect teacher data with respect to intervention components at the comparison schools. This may led to underestimation of effects, if the existing practices at comparison schools are similar to the intervention.

A second limitation is the lack of random allocation of the intervention between schools, which may introduce selection bias. However, analysis of the study sample and the research setting population showed that the study sample was representative of the population. Randomisation is not always possible when conducting school-based interventions [50]. First, there are a limited number of Danish vocational schools. Second, the schools involved in the development phase became intervention schools. This was necessary because the development phase facilitated the implementation, with time spent on internal organisation and integrating the intervention into the pre-existing school practices [51, 52]. We selected comparison schools in order to balance groups on important variables, such as type of basic course. Nevertheless, one basic course was included in the intervention group after selection of comparison schools. Whether unbalanced student characteristic impact outcomes will be examined and potentially controlled for in the analyses.

A third limitation is the time frame for baseline data collection. One substantially important design choice for the study was to collect baseline data during class in the first days of school – i.e., after the onset of the intervention – and this may contribute to underestimation of effects. When interpreting the results of the effect evaluation, the time frame for baseline data will be taken into account in the analyses.

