## Methods

### Study design

Shaping the Social employed a non-randomised cluster controlled design with four intervention schools and six comparison schools. Comparison schools continued with their usual practice.

Intervention schools were selected by convenience sampling; the four schools involved in the development phase of the intervention agreed to become intervention schools. We chose this strategy in order to facilitate the implementation. The four intervention schools are located in major towns dispersed in Denmark and the schools are characterized as being large schools and offering a large range of technical or agricultural basic courses, for example carpenter and zookeeper. Characteristics of the intervention schools were used to select comparison schools among schools with the best match. However, a straight matched-pair design was not possible. Vocational schools in Denmark were ranked according to the following criteria: (1) at least one basic course offered for inclusion in the intervention group, (2) large school size (student population ≥ 800), (3) urban/suburban. Sixteen vocational schools were eligible. Subsequently, eight comparison schools were selected by geographic diversity. Letters explaining the study were sent to the school management, and schools expressing an interest (*n* = 7) were then visited individually. One school withdrew due to the time commitment entailed in the data collection. After selection of comparison schools, one intervention school wanted to include agricultural basic courses, which we accepted; however, the comparison schools were not selected on this criterion.

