### Data collection

The students answered a questionnaire within the first week of their basic course (T0) and at 10-week follow-up (T1). Teachers of the classes that were involved in the intervention answered a questionnaire about implementation at 10-week follow-up. School dropout rates will be tracked via national education registers [28] through a 2-year follow-up period (T2). Table 1 presents an overview of the collected data and the study time path. All residents in Denmark have an unique and permanent personal identification number, which allows individual-level linkage between nationwide registries [29]. In the baseline and 10-week follow-up questionnaire, the students were asked for their personal identification number in order to match the responses between the data collections and to follow up on individuals in registers.

**Table 1 Tab1:** Collection of data and time path

	Instrument	Baseline	Follow-up	
		T0	T1	T2
			10 weeks	2 years
Personal characteristics				
Sex, age, ethnic origin, ethnic identity, parental education [44], family social class, distance to school, living arrangement, having children, quantitative and qualitative aspects of social relations [36], health and health behaviour [36], level of Danish reading and writing, level of prior schooling, prior academic achievement and academic self-efficacy [45]	Self-reported	X		
Primary outcomes				
Student well-being [33]	Self-reported		X	
Cigarette smoking [36]	Self-reported	X	X	
School dropout	Register data			X
Secondary outcomes				
Life satisfaction [39], physical and psychological symptoms [37], loneliness [38], alcohol consumption, use of cannabis and other illicit drugs [36]	Self-reported	X	X	
Immediate outcomes				
Indicators of well-conducted introduction period	Self-reported	X	X	
Indicators of classroom management [33]				
Degree of implementation				
Preliminary meeting at the school with a specialist teacher, the students and their relatives	Teacher reported		X	
Welcoming activities at first school day	Teacher reported		X	
Timetable with a clear description of course, time and clothing requirements	Teacher reported		X	
Class meeting every morning including beverages or food	Teacher reported		X	
Scheduled breaks	Teacher reported		X	
Created a place for hanging out during breaks	Teacher reported		X	
Monthly events during school hours organised across sections, and followed by an open café	Teacher reported		X	

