### Sample size

Sample-size calculation was performed to determine the number of classes needed in order to be able to detect a difference between the intervention and comparison group with respect to student well-being, smoking and school dropout [46]. From a nationwide student satisfaction survey in 2010 at Danish vocational schools, we selected measures on daily smoking (yes, no), consideration of dropping out (yes, no), and two indicators on student well-being: solidarity among students (yes, no), and a positive welcoming atmosphere created by the school (yes, no). Overall, 41 % were daily smokers, 19 % considered dropping out, 17 % reported a lack of student solidarity, and 21 % reported a lack of a positive welcoming atmosphere. We estimated the intra-class correlation to 0.006 for welcoming atmosphere, 0.05 for student solidarity and smoking, and 0.016 for dropout considerations. With a desired power of 80 %, a 5 % significance level, a two-sided test, and an expected 20 % reduction for each outcome in the intervention group, the minimum number of classes in intervention and comparison groups was calculated as ranging from 60 to 110. To be conservative, we chose the highest number of clusters (i.e., classes, *n* = 110). Another necessary assumption for the power calculation was that each class had an average of 20 students. Allowing for 20 % non-respondents, a total of about 5,280 students needed to be included.

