### Evaluation methods

Initially, we will conduct scale validation of the student well-being outcome measure, which we hypothesise to be a four-factor model. Intervention effects will be evaluated by multilevel regression methods, specifically, a multilevel regression analysis accounting for the hierarchical data structure with students nested within classes in which the intervention was implemented, and classes nested within college units. We will use mediation analyses to explore the extent to which any intervention effects are mediated by changes in the measured immediate intervention impacts. The analyses will be conducted for the total study population. The smoking analysis will be repeated whereby students are analyzed according to their baseline smoking status. Analysis of subgroups will be conducted defined by age, parental socioeconomic status and basic course. To assess the stability of the available case analyses, handling of missing data will be conducted and analysis of loss to follow-up will indicate which variables to include.

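### Well-being and dropout are compared only after the intervention, between convenience-chosen schools, so pre-existing school differences cannot be separated from intervention effects

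*Protocol article*

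**What the plan says.** The Protocol article, Study design, describes a "non-randomised cluster controlled design with four intervention schools and six comparison schools". On how the intervention schools came in, it says: "Intervention schools were selected by convenience sampling; the four schools involved in the development phase of the intervention agreed to become intervention schools". Comparison schools had to offer at least one of the basic courses, have 800 or more students and lie in an urban or suburban area. Sixteen qualified. "Subsequently, eight comparison schools were selected by geographic diversity"; seven showed interest and one of these withdrew. No criterion concerns earlier dropout or well-being.

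Table 1 marks well-being at T1 (10 weeks) only, smoking at T0 and T1, and dropout at T2 (two years) only. Under Data collection, "School dropout rates will be tracked via national education registers" for the study's students. Study strengths and limitations describes the choice "to collect baseline data during class in the first days of school", states that this is after the intervention had begun, and names underestimation as the possible consequence.

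The same section concedes that the lack of randomisation may cause selection bias and replies that the study sample was representative of the population. It adds that imbalance in student characteristics will be examined and may be adjusted for. The Abstract says that baseline differences will enter the analysis. Under Evaluation methods, "Intervention effects will be evaluated by multilevel regression methods", with students in classes and classes in college units. No term for an earlier outcome level is mentioned.

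**The concern.** The schools in the intervention arm differ from the others in at least one known way: they were engaged enough to co-develop the programme. A school with a better climate or lower dropout before the study would look like a success without any effect. A school with a worse starting point would hide a real effect. For two of the three primary outcomes, nothing measured before onset shows which of these applies.

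What is at stake is the causal reading of the well-being and dropout results. A systematic difference between the arms does not shrink when more students are enrolled, and a correct standard error does not remove it.

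**Working it through.** **1. Outcome information available before onset (Table 1; Study strengths and limitations)**

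| Primary outcome | T0 (first week, after onset) | Later | Value before onset |
|---|---|---|---|
| Student well-being | none | T1 | none |
| Smoking | yes | T1 | T0 value, taken just after onset |
| Dropout | none | T2 | none |

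The point therefore concerns well-being and dropout, not smoking.

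**2. What a post-only contrast estimates.** Let τ be the effect, and let μ_I and μ_C be the levels that the two sets of schools would have without the intervention. The contrast estimates τ + (μ_I − μ_C). With a pre-period, (I_post − I_pre) − (C_post − C_pre) estimates τ plus any difference in trend, which is zero if trends are parallel.

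Two hypothetical cases, near the dropout of about half given in the Background:
- Intervention schools 45%, comparison schools 50%, in both periods; τ = 0. Post-only: 45 − 50 = −5 points. With the pre-period: (45 − 45) − (50 − 50) = 0.
- Intervention schools 55% before and 50% after; comparison schools 50% in both periods; τ = −5. Post-only: 50 − 50 = 0. With the pre-period: (50 − 55) − (50 − 50) = −5.

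The error can thus go in either direction.

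**3. Does representativeness answer it?** The article's own figure reproduces. Expected males = 5794 × 18311/22511 = 4713.0. With a finite-population correction the half-width is 1.96 × √(5794 × 0.8134 × 0.1866 × (1 − 5794/22511)) = 50.1, which gives 4662.9 to 4763.1 as in Table 2. But Table 2 pools both arms and covers sex, age, prior education and ethnicity, not well-being or dropout.

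A pooled match is also compatible with arms that differ. The baseline shares are 2329/5700 = 0.409 and 3371/5700 = 0.591. Suppose intervention schools lay 5.9 points below the national level on some characteristic and comparison schools 4.1 points above it. The pooled deviation would be −0.409 × 5.9 + 0.591 × 4.1 ≈ 0, with the arms 10 points apart.

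**4. Does student adjustment answer it?** It can balance who enters the schools, as far as that is measured. It does not carry a school's own earlier climate or dropout rate. First-week items about the school may also already reflect the welcoming activities, which are part of the intervention.

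**5. Can the size be derived?** No. The nearest available yardstick is the chance spread between schools. Take SD = √(ICC × p(1 − p)), and for the difference between means of 4 and 6 schools multiply by √(1/4 + 1/6) = 0.645, then by 1.96. Inputs are from Sample size. Assume that 100% or 10% of the ICC lies at school level; 10% multiplies the result by √0.1.

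- Dropout considerations, p = 0.19, ICC 0.016: SD 0.0496; difference 0.0320; ±6.3 points at 100%, ±2.0 at 10%. Planned effect: 0.20 × 19 = 3.8 points.
- Lack of solidarity, p = 0.17, ICC 0.05: SD 0.0840; difference 0.0542; ±10.6 points at 100%, ±3.4 at 10%. Planned effect: 0.20 × 17 = 3.4 points.

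These figures show only that differences between schools could be as large as the planned effects. They describe chance variation among exchangeable schools, which a school-level standard error would cover. They are not an estimate of selection bias.

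**The case against.** Much can be said for the plan. It names selection bias itself and gives reasons for not randomising. Comparison schools were chosen on course, size and location. Baseline adjustment is planned, and the T0 survey is rich: prior achievement, academic self-efficacy, earlier school satisfaction, social support and more. Prior achievement and earlier school satisfaction describe the time before enrolment, so the late T0 does not contaminate them. The article explains that assessment before school start was not possible, and new students could hardly rate classmates and teachers they had not met. A journal article also leaves modelling detail to a fuller plan.

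All of this stands and limits the point. A reader might infer that the plan takes pre-existing differences for intervention effects. It does not: it admits the risk and plans adjustment. A reader might also call the schools self-selected, but the text describes convenience sampling of schools that then agreed.

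The yardstick above has further limits. The sample-size section treats classes as the clusters, so placing the whole ICC at school level is an extreme. Considering dropping out is a survey answer, not the register outcome.

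What the objection does not reach is the absence of any earlier school-level value for two primary outcomes, and the use of pooled representativeness as a reply to selection bias. That reply stands in the article's own text, so it is not a matter of omitted detail.

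**Conclusion.** The point holds as a limit on interpretation. For well-being and dropout, the design cannot separate pre-existing school-level differences from intervention effects. Student-level adjustment may reduce the problem but cannot remove it, and pooled representativeness does not bear on it. The direction is open, and the size cannot be derived from the article.

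A stronger reading is tempting: that usable earlier data for both outcomes were at hand and passed over. The article does not support this for well-being. It uses a 2010 nationwide student survey for sample size, but does not say that the file covers or identifies the ten schools. Its yes/no items are also not the four well-being scales. For dropout the case is better, because the outcome already comes from national registers and the article still writes of that follow-up as work to come. Even there, the article does not state that school and course can be identified in the extract, so the remedy depends on that.

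**What to change.** **Dropout.** If the register identifies school and course, extract the cohorts that entered the same basic courses at the ten schools in the years before the development phase. The article does not date that phase, so the sponsor should fix the window from its own records before looking at outcomes. Report a supporting analysis that adjusts for the pre-period dropout rate of each school and course, or a difference-in-differences (arm by period), and state the parallel-trends assumption. For the latter, define entrants in the same way in both periods: the study students are survey respondents (73% and 81% of those assumed eligible), whereas a register cohort would contain all entrants.

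**Well-being.** State that the result is a post-only comparison, open to school-level selection bias in either direction. Using the 2010 survey is optional, and only if it identifies the study schools.

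**Text.** Stop citing representativeness of the pooled sample as an answer to selection bias.

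**Cost.** One more register extract and a short addition to the plan, with no student contact. The price in interpretation is reliance on parallel trends, which ten schools can test only weakly.

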## Conclusions

Research on the effectiveness of interventions that incorporate a perspective on health behaviour and the social environment for students at vocational schools are of substantial importance. We have demonstrated evaluation strategies of such an intervention, developed to address the school setting rather than individuals, including considerations of implementation and analysis.

### Ethical issues

The study was carried out in accordance with current Danish rules of ethics and legislature and has been approved by the Danish Data Protection Agency, 8 August 2011, record number 2011-54-1265. The National Committee on Health Research Ethics concluded that formal ethics approval was not required because no human biological material was sampled. There is no formal institution for ethical assessment and approval of register- and questionnaire-based population studies in Denmark.

### Consent procedure

When schools were invited to participate, written information was send to the school targeting the school management explaining the implications of participation in the study and we received approval of the student surveys. The study was introduced to students as a study about well-being, health behaviour and health with focus on preventing school dropout in all students. The students were informed that participation was voluntary, that their information would be used for research purposes only and treated confidentially and of the possibility of withdrawing during the study. A few students (1.7 %) were aged 15; otherwise the students were aged 16 or older. Based on Danish legislation and ethical constraints, young people aged 15 or older can make an independent decision to participation in surveys without parental consent [53].
